### 2.8. Statistical Analysis

The Statistical Package for the Social Sciences (SPSS) 25.0 will be employed for data analysis. Descriptive statistics will be conducted to derive summary and dispersion measures of the data. Subsequently, the variables will be subjected to Shapiro–Wilk tests to assess normality and Levene’s tests to evaluate homogeneity of variance.

#### 2.8.1. Intention-to-Treat Analysis

The statistical analysis plan is outlined as follows: Following verification of the effectiveness of randomization, mixed regression models will be employed, with each outcome variable serving as the dependent variable and interventions treated as fixed effects (1 = EG and 0 = CG). Models will be adjusted for baseline values, age, and classroom. Absolute differences in variable changes between baseline and final measurements will be reported as results. For dichotomous dependent variables, odds ratios will be calculated. Sensitivity analyses will involve multiple imputation techniques to address missing measurement values. Five databases will be imputed and analyzed in parallel. In the event of imbalances threatening group comparability, propensity scores will be utilized to control for covariate imbalances. Analyses will be conducted from an intention-to-treat perspective, where subjects remain in the analysis group (EG or CG) to which they were originally assigned, regardless of their intervention compliance. The results will be considered statistically significant at *p* < 0.05.

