### 2.3. Sample Size Calculation

While feasibility trial results typically inform sample size calculations for scalability cluster randomized trials, an approximate sample size estimate is required for budgeting this large-scale trial. The sample size was determined to be 3 clusters (classrooms) per condition (n = 6 clusters) using the GRT sample size calculator from the NIH (researchmethodsresources.nih.gov). This calculation considered an absolute difference of 3% (alpha error of 0.05 and statistical power of 0.80) between the experimental group (EG) and control group (CG) in mean body fat percentage (with a standard deviation of 5), an average of 30 participants in each cluster, and a variance inflation factor of 1.05 based on prior research findings. Following the feasibility study and informed by qualitative research insights, adjustments will be made to refine the MOV-ES intervention.

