### 2.4. Randomization and Blinding

All schools in the city of Talca, Chile, are electronically randomized to select three high schools located in the urban area of Talca (1 public, 1 private subsidized, and 1 private unsubsidized). Each high school will have an EG (n = 30) and a CG (n = 30; no intervention). This selection approach is in line with the Chilean educational system, which associates school administration with the socioeconomic level of families.

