### 2.6. Intervention

The CG will participate in the initial and final measurements but will not receive any intervention, attending their traditional physical education classes. On the other hand, the EG (MOV-ES) will receive an educational intervention within their physical education class. The contents of this intervention involve intrapersonal (benefits of active transportation and safety on the way to school), interpersonal (family safety), organizational, community, physical-environmental, and political (safety, infrastructure, and quality) factors [79]. The program will comprise a weekly session lasting 60 to 90 min each, spanning a total of 16 weeks. The entire intervention program was conducted during school hours within the framework of physical education classes and hosted on the premises of each respective institution. The curriculum will be structured into didactic units, which are divided into 16 subtopics that will be addressed in each of the sessions. Each session will have the following structure: (i) audiovisual presentation; (ii) application of content; and (iii) practical work. The contents will be complemented by the presentation of graphic and audiovisual materials together with practical components in the school space.The contents will follow the recommendations for active transportation interventions in schoolchildren [75] and the material available from the PACO Project (http://profith.ugr.es/pages/investigacion/recursos/manualbici, accessed on 20 June 2024). A summary of the progression and unit structure of the MOV-ES interventions is presented in Table 1.

The sessions of the last month of intervention will include practical activities in bicycle mechanics and walking in the school environment (outside the school). Depending on the possibilities of each school, cycling sessions will be included. At the end of the intervention, and to motivate students to engage in active transportation, both EG and CG participants will receive educational infographics.

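### Section 2.8.1 lists classroom as an adjustment term without saying that it is the random effect; fitted as a covariate it aliases the intervention, and fitted as random it needs about 4 degrees of freedom

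*Protocol article*

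**What the plan says.** Section 2.8.1 of the protocol article states that "mixed regression models will be employed, with each outcome variable serving as the dependent variable and interventions treated as fixed effects (1 = EG and 0" for the control group. The next sentence reads "Models will be adjusted for baseline values, age, and classroom". No random effect is named, and the section does not say whether classroom enters as fixed or random.

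The design is described elsewhere:
- Section 2.3 makes the classroom the cluster: "The sample size was determined to be 3 clusters (classrooms) per condition (n = 6 clusters".
- Section 2.4 places both arms in each of the three schools: "Each high school will have an EG (n = 30) and a CG (n = 30; no intervention".
- Section 2.6 delivers the programme to the class as a group: "the EG (MOV-ES) will receive an educational intervention within their physical education class".

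Together these imply six classrooms of about 30, one per arm in each school, each classroom wholly experimental or wholly control. This is an inference. Section 2.4 does not name the unit that is allocated within a school, but the cluster count in section 2.3 leaves no other coherent reading.

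**The concern.** Classroom stands in one list with two ordinary fixed covariates. A classroom that belongs entirely to one arm cannot be a fixed covariate in a model that is also meant to estimate the arm effect, because the classroom terms already contain the arm. The word mixed suggests that something is random, but not what. Section 2.1 describes a repeated-measures design, so an analyst could make the student random and leave classroom fixed.

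Two analysts could therefore follow the same paragraph and report different effects and p-values for every outcome, including both primary ones. Even with classroom random, the reference distribution matters with only six clusters, and the sample size in section 2.3 already relies on the small-sample one.

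**Working it through.** **Inputs.** From section 2.3: difference 3 points, alpha 0.05 (taken as two-sided; the sidedness is not stated), power 0.80, SD 5, m = 30 per cluster, variance inflation factor (VIF) 1.05, 3 clusters per arm. The VIF implies an intraclass correlation (ICC) of (1.05 − 1)/(30 − 1) = 0.0017. No other ICC is given.

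**1. The plan's own sample size.** Clusters per arm: g = (t₀.₉₇₅ + t₀.₈₀)² × 2 × SD² × VIF / (Δ² × m), with df = 2(g − 1).
- On 4 df: (2.776 + 0.941)² × 2 × 25 × 1.05 / (9 × 30) = 2.69, rounded up to 3. The stated figure reproduces.
- Power at 3 per arm: noncentrality 3/√(2 × 25 × 1.05/90) = 3.93; on 4 df, power is 0.83.
- The normal formula gives 43.6 × 1.05/30 = 1.53, rounded up to 2. The stated 3 therefore rests on 4 df.

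**2. Classroom as a fixed covariate.** Intercept + arm + 5 classroom indicators is 7 columns with rank 6; with baseline value and age it is 9 columns with rank 8. With a control class as reference, arm equals the sum of the three experimental-class indicators, so its coefficient is not estimable. Suppose the software keeps arm and zeroes the indicator of one experimental class. The arm coefficient is then the covariate-adjusted difference between that class and the reference control class. There are 3 × 3 = 9 such pairs and so nine possible answers. The test of any of them omits between-classroom variance: simulated type I error is 5.6% at ICC 0.0017, and 8.4%, 12.2% and 21.7% at assumed ICCs of 0.01, 0.02 and 0.05.

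**3. Classroom as a random intercept.** The fixed part (intercept, arm, baseline value, age) has 4 columns and rank 4, so the effect is estimable. The arm comparison has 6 − 2 = 4 between-classroom df.
- Class means on a normal reference: P(|t₄| > 1.96) = 12.2%, whatever the ICC.
- Class means on t with 4 df: 4.7% to 5.2% in simulation.
- A REML fit behaves differently at small ICCs, because its classroom variance is estimated as zero in about 56% of null trials at ICC 0.0017. In the balanced case its squared standard error is MSB × 2/90 when MSB > MSW, and otherwise uses the pooled (4 MSB + 174 MSW)/178. Drawing these mean squares 400,000 times with no effect, the normal reference rejects 4.2% at ICC 0.0017, 7.2% at 0.02 and 9.7% at 0.05. Referring the same statistic to t on 4 df rejects 0.5%, 1.5% and 2.8%. With a true difference of 3 at ICC 0.0017, its power on 4 df is 0.79.

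**4. Clustering ignored.** Type I error = 2 × [1 − Φ(1.96/√VIF)], with VIF = 1 + 29 × ICC.

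| ICC | Source | VIF | Type I error |
|---|---|---|---|
| 0.0017 | section 2.3 | 1.05 | 5.6% |
| 0.01 | assumed | 1.29 | 8.4% |
| 0.02 | assumed | 1.58 | 11.9% |
| 0.05 | assumed | 2.45 | 21.1% |
| 0.10 | assumed | 3.90 | 32.1% |

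**5. School as a fixed stratum.** Arm is then tested on 2 df. With the noncentrality unchanged at 3.93 (schools assumed to explain no variance), power is 0.55.

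**The case against.** The strongest reply is that a mixed model has at least one random term, that the intervention is expressly the fixed one, and that classroom, the cluster in section 2.3, is the only grouping factor listed. On that reading the effect is estimable. This stands, and a reader who concluded that the effect cannot be estimated as the plan is written would go too far. What remains is that the text does not settle the reading, and its list puts classroom among fixed covariates.

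A reader might also infer that the plan's type I error is 8% to 32%. The document does not support that. It keeps classroom in the model and nowhere proposes dropping it, and the higher rates need ICCs that it does not give. At its own VIF, ignoring clustering costs about half a percentage point. That VIF was set for body fat, however, and no value is given for executive function or the other outcomes.

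Finally, a df method is detail that an article may leave to an analysis plan that is not shown. Its absence alone would be no finding. It is raised here because the printed sample size depends on 4 df and because clarifying the role of classroom leads directly to it. The absence of school from the model is not treated as a fault.

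**Conclusion.** The point holds as a badly fixed model term. Taken as the covariate that the list makes it, classroom exactly aliases the intervention and leaves an arbitrary two-class contrast. Taken as random, it gives an estimable effect whose test should rest on the same 4 df as the sample size. On a normal reference, a class-mean comparison rejects about 12%. A REML fit is close to nominal at the plan's ICC and exceeds 5% at the larger assumed ones.

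This rests on whole-classroom allocation, which is inferred, and on six balanced classes of 30. The ambiguity affects every outcome and should be removed before analysis. It does not show that the trial is unanalysable or that its error rate is badly inflated.

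**What to change.** In section 2.8.1, state that arm, baseline value and age are fixed effects; that classroom is a random intercept and never a fixed covariate; and that arm is tested, with its confidence interval, on between-classroom df fixed at 4, also when the classroom variance is estimated as zero. State in section 2.4 that whole classrooms are allocated. A model with school as a fixed stratum may be reported only as a sensitivity analysis, with its 2 df and power of about 0.55 disclosed.

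The edit is a sentence in each section. The statistical cost is wider intervals than a student-level analysis would give. With REML and 4 df throughout, the test is also conservative when the ICC is very small (about 0.5% at ICC 0.0017), and power at the design values is about 0.79 rather than 0.83. If that matters, letting the classroom variance component go negative reproduces the class-mean t test in the balanced case, which holds its 5% level and the 0.83.

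### Five imputed databases are too few for a reproducible missing-data check when a result lies near p = 0.05

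*Protocol article*

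**What the plan says.** All of this stands in section 2.8.1 of the protocol article. The main analysis is a regression in which "mixed regression models will be employed, with each outcome variable serving as the dependent variable", with group as a fixed effect. "Models will be adjusted for baseline values, age, and classroom". On missing data the section says "Sensitivity analyses will involve multiple imputation techniques to address missing measurement values", and then "Five databases will be imputed and analyzed in parallel". Results are judged against a 0.05 threshold. No other missing-data analysis is named. The section gives no expected amount of missing data and does not describe the imputation model, the seed or the pooling rule.

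**The concern.** A multiply imputed estimate is an average over random draws. With few draws, a rerun of the same analysis on the same data with another seed gives a somewhat different estimate and p-value. The usual defence of five imputations is statistical efficiency. Efficiency shows that the standard error is hardly inflated. It does not show that two analysts with different seeds would report the same side of 0.05.

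The plan applies its model to every outcome: body composition and three executive-function tests as primary measures (section 2.7.1), and a long list of secondary measures (section 2.7.2). With that many comparisons, some p-values near 0.05 are plausible. For those, the check meant to show whether missing data matter could give an answer that depends partly on the seed.

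**Working it through.** **Inputs from the article.** Section 2.8.1 gives m = 5. Section 2.3 gives 3 classrooms per arm, "an average of 30 participants in each cluster, and a variance inflation factor of 1.05 based on prior research findings", "an absolute difference of 3% (alpha error of 0.05 and statistical power of 0.80" and a standard deviation of 5. No missing-data rate is given, so the fraction of missing information (FMI) is assumed at 0.1, 0.2 and 0.3. A two-sided alpha is also assumed.

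**The plan's own figure first.** The SE of the difference is 5 × √1.05 × √(2/90) = 0.764. With a t test on 4 degrees of freedom (df), power at 3 classrooms per arm is 0.83. With 2 per arm it is 0.42. Three per arm is therefore reproduced. The variance inflation factor implies an intraclass correlation (ICC) of 0.05/29 = 0.0017.

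**Efficiency.** Relative efficiency is 1/(1 + FMI/m). At m = 5 it is 98%, 96% and 94% for FMI 0.1, 0.2 and 0.3. Rubin's rules add the B/m term to the variance (B is the between-imputation variance), so a small m is paid for in the standard error.

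**Seed-to-seed SD of the pooled estimate.** In units of its SE this is about √(FMI/m):

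| FMI (assumed) | m = 5 | m = 20 | m = 50 |
|---|---|---|---|
| 0.1 | 0.14 | 0.07 | 0.04 |
| 0.2 | 0.20 | 0.10 | 0.06 |
| 0.3 | 0.24 | 0.12 | 0.08 |

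A slightly finer form is √(B/m) with B = FMI × T/(1 + 1/m), where T is the total variance. At FMI 0.2 it gives 0.183 for m = 5 and 0.063 for m = 50.

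**What this does to a p-value near 0.05.** Take z = 2.0 and FMI 0.2, with a 95% range over seeds under the normal approximation.

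- m = 5: 2.0 ± 1.96 × 0.183 = 1.64 to 2.36, so p runs from 0.10 to 0.02.
- m = 50: 2.0 ± 1.96 × 0.063 = 1.88 to 2.12, so p runs from 0.06 to 0.03.

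On 4 df, as in the sample-size check, the borderline value is t = 2.776. With the √(FMI/m) form at FMI 0.2, m = 5 gives 2.776 ± 0.392 and p from 0.08 to 0.03. With m = 50 it gives 2.776 ± 0.124 and p from 0.06 to 0.04. The ranges are narrower, but the pattern is the same.

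**Simulation.** Six classrooms of 30, SD 5, baseline correlation 0.8 (assumed), outcomes missing completely at random, 10-30% missing, m = 5. At ICC 0.0017 the seed SD is 0.07-0.13 body-fat points, or 0.12-0.22 SE. As a share of the SE it falls when the ICC is higher, to 0.06-0.15 at an assumed ICC of 0.10. A separate simulation at ICC 0.02-0.10 gave 0.07-0.16 SE with m = 5 and 0.02-0.06 with m = 50.

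**A result at the planned effect.** t = 3/0.764 = 3.93. Allowing for FMI 0.2, 3.93 × √0.8 = 3.51. A seed range of ±0.392 gives 3.12 to 3.91, which on 4 df is p = 0.035 to 0.017. The verdict does not change.

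**The case against.** The strongest reply is that this is a sensitivity analysis, that efficiency is already 94-98%, and that the seed matters only on the knife edge. At the planned effect of 3 points the verdict holds whatever the seed. The main mixed models, adjusted for baseline, age and classroom, already give protection when missingness depends on those variables. All the sizes also rest on an assumed missing rate. Each of these statements is correct, and together they make the point minor. They do not justify keeping five: the number is fixed in the text, it ignores the amount of missing data, and a larger one costs almost nothing.

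A reader might infer two stronger things. The first is that classroom is left out of the imputation, so that the standard error comes out too small. The article does not say so. It puts classroom in the analysis model and is silent on the imputation model, which an article may leave to the full protocol or analysis plan. Even with classroom omitted, the simulation at the plan's implied ICC of 0.0017 shows no understatement: mean SE 0.54, 0.57 and 0.61 against empirical SD 0.51, 0.52 and 0.60 at 10%, 20% and 30% missing. A shortfall of 13-22% appears only at an assumed ICC of 0.05, and of 15-25% at 0.10. The second inference is that m = 5 itself understates the standard error. It does not, because Rubin's rules account for the small m.

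**Conclusion.** The point holds as a minor one about the number of imputations. Five databases, fixed regardless of how much is missing, leave a seed-to-seed SD of about 0.14-0.24 SE at 10-30% missing information. With 50 this falls to about 0.04-0.08 SE. The practical effect is confined to sensitivity results near p = 0.05, whose verdict can change on a rerun. Results well away from 0.05 and the primary analysis stand as they are. The sizes rest on the assumed missing information and, in the simulations, on a baseline correlation of 0.8 and data missing completely at random. No claim is made that the planned standard error is too small or that classroom is missing from the imputation.

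**What to change.** In section 2.8.1, replace five with at least 50 imputed databases and state that the results are pooled by Rubin's rules into one estimate. The cost is one sentence and minutes of computing. Twenty would already halve the seed variation, since √(5/20) = 0.5. Fifty brings it to about a third, since √(5/50) = 0.32.

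Optionally, when the imputation model is written down, carry over the classroom adjustment that the analysis model already has. Do not enter arm together with a full set of classroom indicators. Classrooms are nested in arm, so an intercept, five indicators and arm make seven columns of rank six. A random classroom effect, or classroom indicators without arm, avoids this. Indicators are conservative here: in the simulation at ICC 0.0017 the mean SE was 0.57, 0.64 and 0.71 against empirical SD 0.51, 0.51 and 0.59 at 10%, 20% and 30% missing.

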## Abstract

The United Nations, through its 2030 Agenda and Sustainable Development Goals, advocates for the establishment of conducive environments for physical activity, following the ecological model. In line with this initiative, active transportation emerges as an accessible, cost-effective, and sustainable approach to augmenting daily physical activity levels. This study protocol endeavors to assess the impact of an active transportation education program rooted in the ecological model on the physical and mental well-being of high school students. Drawing upon scientific insights, we hypothesize that a 16-week active transportation intervention will lead to a 3% reduction in average body fat percentage and a noteworthy enhancement in executive function (including inhibition, cognitive flexibility, and working memory), physical fitness (comprising cardiorespiratory fitness and muscle strength), and mental health (encompassing mood disorders and cognitive functioning). If this intervention proves effective, it could offer a viable solution for the school community, especially in reducing congestion within the school environment. The study protocol aims to evaluate the impact of an active transportation educational program based on the ecological model on the physical and mental well-being of high school students. Three high schools located in the urban area of Talca, Chile, will be randomly selected (one public, one privately subsidized, and one private non-subsidized). Each high school will be randomly assigned an experimental group (n = 30) and a control group (n = 30; without intervention). The experimental groups will receive an active transportation educational intervention during their physical education classes for four months (60 to 90 min sessions, once a week), while the control group will receive no intervention. The primary outcome will provide information on body composition and executive function. Secondary outcomes will include objective physical activity level, physical fitness, mental well-being, academic achievement, health-related quality of life, perception of environmental urban features, physical activity barriers, and adherence to active transportation. It is expected that the results of the MOV-ES Project will transcend the physical health of schoolchildren and will have an impact on the school community, especially by decongesting the school environment.

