#### 2.7.1. Primary Outcomes

The primary variables and the selected instruments for their measurement are summarized in Table 2. In addition to sociodemographic variables (such as birth date and gender), the following information will be collected from each participant at baseline:

Body composition: The percentage of fat mass and fat-free mass will be obtained using eight electrodes of tetrapolar bioimpedance (InBody 570^®^, Body Composition Analyzers, Seoul, Republic of Korea). Prior to the assessments, students will be asked to come to the measurement in light clothing, without metal-containing garments, and with the possibility of removing their footwear. This whole process will be carried out under the supervision of a school teacher.

Executive function: The NIH Toolbox for Assessment of Neurological and Behavioral Function^®^ (NIH Toolbox^®^ in Spanish, v. 1.8) was created as a comprehensive set of neurobehavioral assessments intended to rapidly evaluate sensory, motor, emotional, and cognitive abilities throughout the lifespan, spanning ages 3 to 85 years, available in both English and Spanish [80]. Inhibitory control and attention will be measured using the Flaker Test of Attention and Inhibitory Control. Cognitive flexibility and attention will be measured using the Dimensional Change Card Sorting Test, and working memory will be measured using the List Sorting Working Memory Test. For each test, the evaluator will read the specific instructions of the test to be applied, making sure, by verbal confirmation, that the subject understands the procedure. The results of the tests are extracted by means of scores.

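### Four distinct measures are primary and each is tested at p < 0.05 with no order or adjustment, while only percent body fat is powered; if any one may carry a primary claim, the family-wise error is up to 18.5%

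*Protocol article*

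**What the plan says.** The abstract of the protocol article sets two primary domains: "The primary outcome will provide information on body composition and executive function".

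Section 2.7.1 fills them in. For body composition: "The percentage of fat mass and fat-free mass will be obtained using eight electrodes of tetrapolar bioimpedance". For executive function there are three separately scored tests. One is a flanker task for inhibition, another is a card-sorting task for flexibility, and for the third the section states that "working memory will be measured using the List Sorting Working Memory Test". No composite score is defined and no lead measure is named.

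Section 2.8.1 fits mixed models "with each outcome variable serving as the dependent variable" and ends with a single criterion: "The results will be considered statistically significant at" p < 0.05. No order of testing, alpha split or adjustment is given.

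Section 2.3 sizes the trial for a 3-point difference between arms "in mean body fat percentage (with a standard deviation of 5"), with alpha 0.05, power 0.80, 30 participants per cluster and a variance inflation factor of 1.05. The result is three classrooms per arm. No effect size, standard deviation or power is given for any executive-function test.

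The last paragraph of the Introduction puts body fat in hypothesis (i), and executive function in hypothesis (ii) together with fitness and mental health. Nowhere does the article say which results, or how many, count as success on the primary outcome.

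**The concern.** A 5% significance level limits the false-positive rate of one test. When four tests all have primary standing, each is judged at 5%, and nothing says how they combine, the probability that at least one is falsely significant is well above 5%. A report could then present one significant executive-function score, with body fat null, as a positive result on a primary outcome, although the trial was not sized for that score and the plan has no rule against it.

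This matters because the Discussion intends the findings to inform ministries and public policy. There is a second effect: with no stated power for executive function, the plan gives no indication of how large an effect on those tests the trial could reliably detect.

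**Working it through.** **1. Reproduce the sample size.** Inputs from Section 2.3: difference 3, SD 5, m = 30 per cluster, VIF 1.05, alpha 0.05 (sidedness not stated; two-sided assumed), power 0.80.

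- Standard error of the difference with g clusters per arm: SE = √(2 × SD² × VIF / (g × m)). For g = 3: √(2 × 25 × 1.05 / 90) = 0.764.
- Ratio: 3 / 0.764 = 3.93, on 2(g − 1) = 4 degrees of freedom.
- Ratio needed for 80% power, as the sum of the t quantiles at 0.975 and 0.80 on 4 df: 3.72. Since 3.93 exceeds it, g = 3 is enough.
- With g = 2 the ratio is 3.21 against 5.36 needed, so it fails.

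Three clusters per arm is confirmed. Power is 84% by the shifted-t formula and 83% by the non-central t. The sample size is sound for its one endpoint on its own assumptions.

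**2. Count the primary tests.** Section 2.7.1 refers to the percentage of fat and fat-free mass. As a percentage, fat-free mass is 100 minus percent fat, so its group difference is the same with the sign reversed and its p-value is identical. It adds no test. Percent body fat plus three executive-function tests gives k = 4.

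**3. Family-wise error with each test at 0.05.** Assume no true effect on any of the four, and that any one significant result may support a primary claim.

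- Independent tests: 1 − 0.95⁴ = 0.185, or 18.5%.
- Correlated tests (multivariate normal simulation, 500,000 draws). The documents give no correlations, so these values are assumptions:

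| Assumed correlation | Among the three executive-function tests only | Among all four measures |
|---|---|---|
| 0.3 | 18.0% | 17.5% |
| 0.5 | 16.9% | 15.6% |
| 0.7 | 15.4% | 13.0% |

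- Counting only the two domains, as if executive function were one test: 1 − 0.95² = 9.75%.

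**4. What an equal split would cost.** At 0.05 / 4 = 0.0125 with three clusters per arm, power for body fat is 36% by the shifted-t formula and 49% by the non-central t. Testing body fat first at the full 0.05 leaves it at 83% to 84%.

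**The case against.** **The rule that any one result suffices is not written anywhere.** This stands. The Introduction numbers body fat and executive function as separate hypotheses, and the Conclusions expect a body-fat reduction together with executive-function gains. If all four measures had to succeed, there would be no inflation. But the article does not say that either, and Section 2.8.1 applies its threshold result by result. The error rates are therefore conditional on a claim rule that the text permits but does not state.

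**An article condenses, and multiplicity rules often sit in a separate plan.** This is fair as far as a missing adjustment goes. However, Section 2.8.1 presents itself as an outline of the statistical analysis plan and does fix a criterion, and the choice of several primary measures is made in the article itself. A later multiplicity rule would change that stated criterion. The finding is the combination of several primaries, one flat threshold and one powered endpoint.

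**Stronger readings that a reader might infer.**

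- An error rate near 23% (1 − 0.95⁵ = 22.6%). This needs fat-free mass to be a fifth test independent of percent fat. Section 2.7.1 most naturally describes a percentage, which is the exact complement. Even if kilograms were meant, independence from percent fat would be an unsupported assumption.
- That a null executive-function result would be uninterpretable. Section 2.8.1 reports absolute differences, and a confidence interval would show which effects are excluded. Only the absence of stated power is supported.
- That every other outcome must become exploratory. Section 2.7.2 already labels them secondary, and the defect does not reach that far.

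**Conclusion.** The concern holds in this form: four distinct primary measures, one unadjusted 0.05 threshold for each, no stated rule for combining them, and a sample size built on percent body fat alone. If one significant measure may support a primary claim, the family-wise error is at most 18.5% for non-negatively correlated tests, and about 13% to 18% under assumed correlations of 0.3 to 0.7. Even the two-domain count gives 9.75%, nearly twice nominal.

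The structural point rests on the text alone and is firm. The percentages rest on three assumptions: the permissive claim rule, correlations that the documents do not give, and each single test holding its own 5% level. The sample size calculation is not in error for the endpoint it addresses; it simply does not cover the other three primary measures.

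**What to change.** Change Section 2.7.1, Section 2.8.1 and the abstract so that:

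1. Percent body fat, the powered outcome, is the first primary test at two-sided 0.05.
2. The three executive-function scores are tested only if body fat is significant, with Holm adjustment across the three (thresholds 0.05/3 = 0.0167, then 0.025, then 0.05).
3. Fat-free mass percentage is not counted as a separate primary.
4. The listed secondary outcomes stay secondary, reported with confidence intervals and without confirmatory claims.

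This holds the error over the four primary tests at 5% and leaves body-fat power at about 83% under the plan's assumptions, with no added participants or measurements. Holm across all four, or a stated requirement that all succeed, would also remove the ambiguity. The ordered scheme is preferred because it is the one that keeps the body-fat test at the level for which it was sized without making success depend on the unpowered tests.

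The cost is real but small: executive function can be claimed only after body fat succeeds, which gives it less standing than the authors now do. The trial is registered and ethics-approved, so those records may need an update. The change should be made before outcome data are seen.
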